### Study intervention

Telephone-based administration of the WHQ will be compared to the ‘gold standard’ (reference test) of in-person assessment at 30 days after surgery by a trained clinician in accordance with the US Centre for Disease Control criteria (Additional file 2). The WHQ will be delivered integrated into the trial pathway for included patients (Fig. 2). The telephone-based WHQ will be performed at 28–30 days (i.e. in the 72 h prior to in-person follow-up) by a non-surgeon researcher, according to a telephone script. Patients will be asked to provide between one and three telephone contact numbers, either personal or belonging to a family member or community worker. The non-surgeon researcher directing completion of the WHQ should be blinded to the outcome of the in-person wound assessment within the FALCON trial. In the event that the patient is unable to be contacted by telephone at 27–30 postoperative days (before in-person follow-up), the WHQ can be performed after the in-person follow-up appointment, where possible. This should be completed by a non-surgeon researcher that is independent of the assessment for the FALCON primary outcome, to ensure independent measures are taken. The process and pathway for telephone follow-up will be co-designed by patient and public partners to optimise successful and culturally sensitive delivery.

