### Primary outcome measure

Proportion of surgical site infections that are correctly identified by the telephone WHQ (in comparison to in-person review), summarised using measures of diagnostic test accuracy

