### Sample size

As TALON-2 is a validation study for a diagnostic criterion, no formal sample size calculation is required. A range of sample sizes and their impact on the 95% confidence interval (CI) around estimates of sensitivity 0.92 and specificity 0.95 based on a prevalence of 0.21 using the binomial exact formula are presented in Table 1. Sample sizes are adjusted to allow for 15% loss to follow-up from the host trials, and 15% of patients who do not achieve both telephone WHQ completion and 30-day in-person follow-up within TALON-2. Sampling from Hub and Spoke centres across several LMICs will give a representative sample of urban and rural settings.

**Table 1 Tab1:** TALON-2 study sample size estimates

Patients recruited to host trial	Patients retained for follow-up	Paired WHQ and in-person follow-up	Patients with SSI^a^	Patients without SSI^b^	Precision around test accuracy measures	
					Sensitivity (95% C.I.)	Specificity (95% C.I.)
714	607	516	108	408	0.92 (0.85–0.96)	0.95 (0.93–0.97)
571	485	412	87	325	0.92 (0.84–0.97)	0.95 (0.92–0.97)
428	364	309	65	244	0.92 (0.83–0.97)	0.95 (0.92–0.97)
285	242	206	43	163	0.92 (0.81–0.99)	0.95 (0.91–0.98)

^a^0.21 * number paired WHQ and in-person follow-up

^b^0.79 * number paired WHQ and in-person follow-up

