### Statistical analysis

Statistical analysis will be undertaken using R Project for Statistical Computing (V3.6.1). The outcome against which the WHQ prediction model will be validated is 30-day in-person wound assessment according to the CDC criteria (binary outcome: SSI/no SSI). Blinded 30-day outcome data for patients included in TALON will be made available by the FALCON Trial Management Group for the purpose of this analysis. Cross-tabulations of the reference CDC diagnosis (‘no SSI’ or ‘SSI’) and a binary variable of the self-assessment WHQ total score (created by a cut-off score; for instance, a WHQ total score of less than or equal to a specified value) will be compared.

Criterion validity will be examined against the reference (face-to-face SSI assessment) to evaluate the performance of WHQ in discriminating between individuals with and those without SSI. Sensitivity and 1-specificity values of the WHQ for different cut-off scores will be used to plot a receiver operating characteristic (ROC) curve. From derivation data in the UK, WHQ cut points of 6 to 8 were found to provide optimal sensitivity and specificity [21]. We will calibrate the tool with a range of cut points from 5 to 9 in order to explore differences in calibration across included countries. The overall ability of the WHQ to discriminate between individuals with and those without SSI will be measured by the area under the ROC curve (AUC), with uncertainty presented using 95% confidence intervals. Diagnostic test accuracy will be presented as sensitivity, specificity, and positive and negative predictive value.

The overall rate of missing data is anticipated to be low. The patients that did and did not receive a 30-day in-person assessment (reference standard) will be compared to assess for partial or differential verification bias. A sensitivity analysis will be performed with missing data imputed using multiple imputation by chained equations to explore the impact of missing data. A full statistical analysis plan has been published online at: https://globalsurg.org/resources/phd-research-projects/talon/.

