There are limitations to the proposed study design. Firstly, due to limitations with travel around the SARS-CoV-2 pandemic, the ability to conduct cognitive interviewing during the adaptation and translation process may be limited. From site researchers and CEI representatives, it was highlighted that video-based interviews with patients in low-resource settings may prove challenging both logistically, and to the richness of the data, and risk of accentuating power imbalances between the researcher and patients. We have modified the proposed methodology to include pragmatic, structured interviews with site researchers; however, further iterative adaptation following face-to-face patient interviews may be required in the future [29]. A mixed-methods approach, including Rasch analysis of pilot cohort data, will further enhance the adaptation and scaling process [68]. Secondly, the Wound Healing Questionnaire has not previously been validated for use across low-resource settings, as such the optimal score calibration is yet to be determined. Whilst a pre-defined range of cut points will be adopted, this combines the calibration and validation phases into a single analysis; this was a pragmatic decision to manage a complex project across global trials in a manageable timeframe. Thirdly, we have not pre-defined thresholds for sensitivity and specificity for that would be acceptable for clinical practice or trial adoption in this protocol. Consensus work is required to define minimally acceptable criteria for diagnostic accuracy during future development and implementation of the WHQ [69]. Fourthly, the WHQ can be administered any time during the 72 h preceding in-person assessment. Whilst there is a theoretical risk that patients could suffer a new SSI event 28 to 30 days after surgery that has not previously manifested, this is clinically improbable and is not supported by existing data [6, 70]. Another risk is that completion of telephone follow-up immediately prior to in-person follow-up may have a deleterious effect on in-person follow-up rates, overestimating the retention benefit. We have designed the TALON case report form and patient information to stress the need for both in-person and telephone follow-up, and can compare rates of attrition to the overall host trial population. Finally, the exploratory use of video follow-up in this study is not the central focus of this work. Whilst this will provide the first available data on video-based follow-up of surgical wounds in LMICs, contributing significantly to understanding of this area, further work is likely to be required to standardise protocols for ‘live’ video assessment and explore its reliability in depth.

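### Questionnaires taken after the in-person visit are treated as independent because the caller is, but the patient answering has already been examined, so these pairs risk biasing the primary accuracy estimate

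*Protocol article*

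**What the plan says.** All references are to the protocol article.

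- **Planned order (Study intervention).** "The telephone-based WHQ will be performed at 28–30 days (i.e. in the 72 h prior to in-person follow-up) by a non-surgeon researcher".
- **Exception (same section).** If the patient cannot be reached before the visit, "the WHQ can be performed after the in-person follow-up appointment, where possible". No upper time limit is stated for this later call.
- **Safeguard (same section).** "The non-surgeon researcher directing completion of the WHQ should be blinded to the outcome of the in-person wound assessment within the FALCON trial". For the later call, the researcher must be "independent of the assessment for the FALCON primary outcome, to ensure independent measures are taken". Centre selection asks for the same separation of staff. Nothing is said about what the patient knows.
- **Source of the score (Statistical analysis).** The reference diagnosis is cross-tabulated with a "binary variable of the self-assessment WHQ total score". Pairs are not distinguished by the order of the two assessments.
- **Primary outcome.** "Proportion of surgical site infections that are correctly identified by the telephone WHQ (in comparison to in-person review"), summarised by diagnostic accuracy measures.
- **Limitations (Discussion).** The fourth limitation concerns timing: "Fourthly, the WHQ can be administered any time during the" 72 h before the visit. It is defended on the ground that a new infection in those days is improbable. The post-visit exception is not mentioned.

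**The concern.** An index test should be obtained without knowledge of the reference result. Here the caller asks and scores, but the patient supplies the information. A separate, blinded caller removes one route by which the reference result can reach the WHQ score. It leaves the other open: a patient examined under the CDC criteria may have been told the finding or been given treatment, and may answer accordingly. The patient may also tell the caller, which would undo the caller's blinding.

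The study asks whether a telephone call can assess the wound remotely. A WHQ answered after the visit is not a test of that use. Under a telephone-only pathway these patients would have been non-contacts in the planned window. Pooling them with the planned pairs puts observations of a different kind into the primary estimate. A confidence interval does not show the resulting error, and a larger sample does not remove it.

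**Working it through.** **1. The plan's own figures.** Sample size gives "estimates of sensitivity 0.92 and specificity 0.95 based on a prevalence of 0.21 using the binomial exact formula", with two successive losses of 15%. For the largest row of Table 1:

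- Retained: 714 × 0.85 = 606.9 (stated 607).
- Paired: 606.9 × 0.85 = 515.9 (stated 516).
- With infection: 516 × 0.21 = 108.4 (stated 108). Without: 516 × 0.79 = 407.6 (stated 408).
- Exact 95% interval for 99/108: 0.848 to 0.961 (stated 0.85 to 0.96). For 388/408: 0.925 to 0.970 (stated 0.93 to 0.97).

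Table 1 reproduces. A pair is counted once both assessments are done, whatever their order. The half-width for sensitivity is (0.96 − 0.85)/2 = 5.5 points.

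**2. Effect of mixing the two kinds of pair.** Let f be the share of post-visit pairs among patients with infection, S0 the sensitivity before the visit and S1 the sensitivity after it.

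Apparent sensitivity = (1 − f) × S0 + f × S1, so bias = f × (S1 − S0).

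Of the inputs, only 0.92 is in the document, as the planning value for sensitivity. The range 5% to 30% for f, the range 0.95 to 1.00 for S1 and the alternative S0 of 0.80 are assumptions. Bias in percentage points:

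| f | S0 0.92, S1 0.95 | S0 0.92, S1 1.00 | S0 0.80, S1 0.95 | S0 0.80, S1 1.00 |
|---|---|---|---|---|
| 5% | +0.15 | +0.4 | +0.75 | +1.0 |
| 10% | +0.3 | +0.8 | +1.5 | +2.0 |
| 20% | +0.6 | +1.6 | +3.0 | +4.0 |
| 30% | +0.9 | +2.4 | +4.5 | +6.0 |

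For specificity, take the planned 0.95 and an assumed post-visit value of 0.97 to 1.00. The bias runs from 0.05 × 0.02 = +0.1 point to 0.30 × 0.05 = +1.5 points, with f now the share among patients without infection. The effect on the AUC was not computed. If treatment or healing makes S1 smaller than S0, the sign reverses.

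**3. Precision lost by leaving post-visit pairs out.** This uses the largest row, sensitivity 0.92, and exact intervals on the unrounded count 0.92 × n, where n is the number with infection. On that basis the full 516 pairs give 0.852 to 0.963.

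- f = 10%: about 464 pairs, 98 with infection, 0.848 to 0.965.
- f = 20%: about 413 pairs, 87 with infection, 0.842 to 0.967.
- f = 30%: about 361 pairs, 76 with infection, 0.835 to 0.970.

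The lower limit falls by at most 0.852 − 0.835 = 1.7 points. The specificity interval at f = 30% is 0.918 to 0.972, against 0.924 to 0.969 for all pairs.

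**The case against.** **The analysis plan may already deal with this.** The article says a full statistical analysis plan is published, and it is not shown here. A reader might infer that post-visit pairs will enter the primary analysis. The documents do not establish that; the article only fails to separate them. What stands without the analysis plan is the article's own text: a rule that permits the reversed order, a reason for independence that does not cover the respondent, and a timing limitation that leaves the exception out.

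**The independence phrase may mean the observer only.** It follows a sentence about who completes the WHQ, and the article nowhere says that the patient is blinded. That reading is fair, and it shows how to correct the wording. It does not make the two measurements independent.

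**The later call serves other outcomes.** It is a fallback, and a late WHQ counts towards return and retention. This stands: the call need not be forbidden. The issue is its use for accuracy.

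**Size and direction.** A reader might infer that accuracy will certainly be inflated, by an amount close to the width of the confidence interval. The documents do not support that. They give neither the share of post-visit pairs nor whether patients are told the finding, and the questionnaire items are not shown. Patients with an infection may already know of it before the visit, which would narrow the gap between S0 and S1. A bias near 5.5 points needs a true sensitivity well below the planned 0.92 together with a large share of late calls.

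**Exclusion has its own cost.** Patients reached only after the visit are harder to reach and may differ from the rest. This stands, and it is why they should appear in a sensitivity analysis.

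**Conclusion.** The concern holds as a risk of bias in the primary outcome. An independent, blinded caller does not make a patient-reported index test independent of a reference examination that the patient has already had. The likeliest direction is towards better agreement, but it can reverse.

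The size cannot be determined from the document. At the planned sensitivity of 0.92 it is about +0.15 to +2.4 points, and at an assumed 0.80 about +0.75 to +6 points. Both ranges assume 5% to 30% post-visit pairs and a post-visit sensitivity of 0.95 to 1.00. At the plan's own value the bias lies inside the 5.5-point half-width of the largest sample. No figure in the article is wrong on this account. The point should be fixed because the remedy is cheap and concerns the primary estimate.

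**What to change.** - Base the primary 2×2 tables, ROC curve and AUC on WHQs completed before the in-person assessment. Report an analysis that adds the post-visit WHQs as a sensitivity analysis, and state how many there are. If the analysis plan already does this, say so in the article.
- Continue to count post-visit WHQs for the return and retention outcomes.
- Confirm that the order of the two assessments and the interval between them are recorded. The Telephone follow-up pathway section does not list the date or time of the call among the data it describes. Study status reports 350 TALON-2 patients already collected, so for them the order must be recoverable from existing records.
- Limit the independence statement in Study intervention to the observer, and add the post-visit exception to the timing limitation in the Discussion.

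The cost is a sentence on the analysis set and two wording changes, plus a check of the data fields. The primary interval widens slightly: with 20% of 516 pairs left out, sensitivity goes from 0.85–0.96 to about 0.84–0.97. Some hard-to-reach patients leave the primary set, and the sensitivity analysis would show whether that matters.

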**Fig. 2 Fig2:**
[figure not shown]
TALON-2 study with a trial patient pathway. WHQ=Bluebelle Wound Healing Questionnaire, SWAT=study within a trial, D30 postoperative day 30 with day 0 as date of surgery

After sufficient data has been collected for the primary validation analysis, an extension to the study intervention will be implemented. Patients will undergo remote telemedical (photo or video) review to track their recovery from surgery and will be invited by the assessor to provide ‘live’ visualisation of the wound to check wound healing (Additional file 3). This will be performed using a locally available video platform as an adjunct to completion of the WHQ in remote wound assessment. No recording or storage of the video data will be undertaken.

### Telephone follow-up pathway

Descriptive data to explore variation in telephone follow-up implementation and procedures between patient groups, centres, and countries will be collected including the number of attempts required to connect, the type of phone used (including whether the phone has a camera or video capability), the phone’s owner, and the language of delivery.

### Primary outcome measure

Proportion of surgical site infections that are correctly identified by the telephone WHQ (in comparison to in-person review), summarised using measures of diagnostic test accuracy

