### Potential solutions for remote surgical site assessment

The Bluebelle Wound Healing Questionnaire (WHQ) has been developed and validated in the UK (English language) to assess post-discharge infections following abdominal surgery (HTA: 12/200/04) and is attractive for use in randomised trials. The WHQ was designed to be either completed by a healthcare professional or self-reported by patients [19] and as such has been described as a ‘universal-reporter’ outcome measure (UROM) [20]. In a UK validation study, the WHQ demonstrated good reliability and excellent discrimination [21–23]. The WHQ was completed both in-person and over the telephone by a healthcare professional trained in wound assessment (e.g. nurse, junior doctor), demonstrating feasibility of telephone delivery. However, no external validation has been performed in LMICs where health literacy, language and cultural contexts, and digital infrastructure differ substantially. If the WHQ can be administered remotely (e.g. over the telephone) with satisfactory diagnostic accuracy, this would reduce resource usage, making surgical research more effective and more sustainable. Other digital adjuncts to surgical site evaluation such as video assessment may further enhance accuracy [24].

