### Justification of study design

Studies within a trial (SWATs) have gained significant attention from trial methodologists and funders over the past 3 years and are now the focus of a Trial Methodology Research Partnership working group (Trial Forge) [25] and National Institute for Health Research (NIHR) funding stream. SWATs exploit the delivery network and infrastructure of major randomised trials to efficiently answer methodological research questions. Ongoing large international trials in global surgery provide a unique opportunity to improve the quality and efficiency of global wound infection research [26].

The overall aim of this study protocol is to evaluate the feasibility and validity of a remote, digital pathway for wound assessment after hospital discharge for patients in low-resource settings.

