### Eligibility criteria

Consecutive adult patients (greater than 18 years) recruited to the FALCON or ChEETAh study that are likely to return for routine in-person follow-up at around 30 days postoperatively are eligible. Consent for an additional telephone follow-up call within the TALON-2 study will be taken at the same time as trial consent, using a targeted Informed Consent Form and Patient Information Sheet. Community representatives will co-produce these resources to ensure culturally appropriate language and delivery.

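### The aim is wound assessment after discharge, but TALON-2 accuracy does not separate infections diagnosed before discharge; fix their status and add an estimate without them

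*Protocol article*

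**What the plan says.** Under Justification of study design, the overall aim is to "evaluate the feasibility and validity of a remote, digital pathway for wound assessment after hospital discharge for patients in low-resource settings". Under Potential solutions for remote surgical site assessment, the Wound Healing Questionnaire (WHQ) is described as built "to assess post-discharge infections following abdominal surgery".

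The TALON-2 sections carry no such limit:

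- **Study objectives.** The first objective is accuracy in detecting abdominal surgical site infection (SSI), with no mention of discharge.
- **Primary outcome measure.** "Proportion of surgical site infections that are correctly identified by the telephone WHQ (in comparison to in-person review").
- **Study intervention.** The reference is "in-person assessment at 30 days after surgery by a trained clinician in accordance with the US Centre for Disease Control criteria".
- **Statistical analysis.** The outcome to validate against is "30-day in-person wound assessment according to the CDC criteria (binary outcome: SSI/no SSI"), and "Blinded 30-day outcome data for patients included in TALON will be made available by the FALCON Trial Management Group".
- **Eligibility criteria.** Host-trial adults "that are likely to return for routine in-person follow-up at around 30 days postoperatively are eligible", and consent for the extra call "will be taken at the same time as trial consent". Infection before discharge is not an exclusion.
- **Sample size, Table 1.** Infections are counted as 0.21 of all paired patients.

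**The concern.** Take a patient whose infection is diagnosed and treated on the ward in the first week and who is telephoned at day 28. The text does not fix how this patient enters the two-by-two table.

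- If the reference is any SSI up to day 30, the patient is a reference positive. A high WHQ score then confirms something the team already knows. A low score, because the wound has healed, counts as a miss.
- If the reference is infection present at the day-30 visit, a patient whose wound has healed is a reference negative. Reporting the earlier episode by telephone then counts as a false positive.

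Neither result shows whether a call finds an infection that nobody has yet recognised. The Discussion names missed infection as a possible harm of unvalidated remote follow-up, and a pooled sensitivity may not give the miss rate for that group. The Statistical analysis section also compares cut points 5 to 9 across countries. If the share of infections diagnosed in hospital differs between countries, for instance through length of stay (an assumption), that mix could look like a difference in calibration.

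**Working it through.** **1. The plan's own figures.** Inputs from Sample size: 15% loss, then a further 15%; prevalence 0.21; sensitivity 0.92; exact binomial intervals. Largest row: 714 × 0.85 = 606.9, printed 607; 606.9 × 0.85 = 515.9, printed 516; 516 × 0.21 = 108.4, printed 108. The exact 95% interval for 99/108 is 0.848-0.961, printed 0.85-0.96. The other rows also reproduce: 80/87 gives 0.841-0.967, 60/65 gives 0.830-0.975 and 40/43 gives 0.809-0.985. Table 1 is sound for all SSIs. It gives no precision for infections not diagnosed before discharge.

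**2. How far the two sensitivities can differ.** Suppose infections diagnosed before discharge are reference positives. Let f be their share of all SSIs, Se_in the WHQ sensitivity in them, and Se_post the sensitivity in the rest. Then

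Se_all = f × Se_in + (1 − f) × Se_post, so Se_post = (Se_all − f × Se_in) / (1 − f).

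Se_all = 0.92 is the planning value. The documents give neither f nor Se_in, so both are assumed and varied:

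| f | Se_in = 1.00 | Se_in = 0.92 | Se_in = 0.80 |
|---|---|---|---|
| 0.1 | 0.911 | 0.920 | 0.933 |
| 0.3 | 0.886 | 0.920 | 0.971 |
| 0.5 | 0.840 | 0.920 | not possible (1.040) |

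For f = 0.3: (0.92 − 0.30)/0.70 = 0.886, and (0.92 − 0.24)/0.70 = 0.971. The miss rate outside hospital would be 11.4% or 2.9%, against 8% pooled. If Se_in equals the pooled value, there is no difference.

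**3. Predictive values.** Under the same reading, leaving out infections diagnosed before discharge changes the prevalence to 0.21(1 − f)/(1 − 0.21f). At f = 0.3 this is 0.147/0.937 = 0.157 rather than 0.21, so the planned positive and negative predictive values would also change. Specificity would not change, apart from any patients still in hospital at the call, because the cases left out are all reference positives. Under the day-30-visit reading, specificity is the measure affected.

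**4. Precision of a second estimate.** From 108 SSIs, f = 0.4 leaves 108 × 0.6 = 65 and f = 0.6 leaves 108 × 0.4 = 43. These match the third and fourth rows of Table 1: 0.83-0.97 and 0.81-0.99, against 0.85-0.96 with 108.

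**The case against.** The strongest reply has three parts.

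First, the aim describes when the wound is assessed, not when the infection began, and the TALON-2 objective and primary outcome agree with each other. A main use of the questionnaire is to replace in-person 30-day review as a trial outcome. For that use, agreement with the 30-day reference in all patients is the accuracy that matters. This stands, and it is why the primary outcome should be kept.

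Second, a reader might infer that the primary outcome definitely counts in-hospital infections. The article does not say so. The CDC criteria are in Additional file 2, the host-trial definitions are reported elsewhere and the full analysis plan is published separately; none is shown here. The remark under limitations in the Discussion, that a previously unmanifested infection arising at 28 to 30 days is improbable, fits a cumulative reading but does not state one. This also stands, so the point is conditional.

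Third, a reader might infer that pooled sensitivity must be optimistic because known infections are easy to report. The documents do not support a direction. The test is a total score above a cut-off, and a healed wound may score low. The items and any recall period are in Additional file 1, which is not shown.

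The objection does not remove the gap. The target condition of the primary outcome is more than an analysis detail, and the article's post-discharge purpose has no estimate of its own.

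**Conclusion.** The point holds in a limited form. The article's post-discharge purpose and its TALON-2 accuracy target are not tied together, because the status of infections diagnosed before discharge is not stated and they are not separated. If they are reference positives, pooled sensitivity need not equal sensitivity for the infections that the remote pathway must find. At a pooled 0.92 and an assumed in-hospital share of 30%, the second figure runs from 0.886 to 0.971 as assumed in-hospital sensitivity falls from 1.00 to 0.80. The difference can be downward, upward or nil.

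It would go too far to say that the planned sensitivity is wrong or does not describe the telephone questionnaire. It remains the sensitivity of the WHQ against the 30-day in-person reference. This is an inexpensive addition to the plan.

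**What to change.** 1. State whether an SSI diagnosed before discharge, including one healed by day 30, counts as a reference positive.
2. Keep all-SSI accuracy as defined under Primary outcome measure.
3. Pre-specify beside it sensitivity and specificity in patients discharged without a diagnosed SSI, and base the conclusion about post-discharge detection on that estimate.
4. Show pre-discharge SSIs as a separate row of the cross-tabulation.
5. Count patients still in hospital at the time of the call separately, including for the telephone contact rate.
6. Take discharge and diagnosis dates from the host-trial record where held. Add a form field only for patients still to be recruited.

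The cost is some outcome and analysis wording, at most a small addition to the form, and a wider interval for the second estimate (working, step 4). Study status reports TALON-2 data already obtained for 350 patients and FALCON recruitment complete. A new field cannot cover those patients prospectively, so their timing data may be incomplete if the host trials did not record it. The number with unknown timing should be reported.
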